## Abstract

*Background*. Early intervention in prediabetes can prevent or delay the incidence of type 2 diabetes mellitus (T2DM). Traditional Chinese patent medicine (TCPM) is widely used in China to prevent T2DM. This study aims to evaluate the efficacy and safety of TCPMs for preventing T2DM. *Method/Design*. This study is a multicenter, cohort study with two arms. A total of 600 participants will be recruited. The participants will be divided into either intervention or control groups according to their own desire, and the exposure factor is the application of TCPMs. All participants will be encouraged to lead a healthy lifestyle, and the intervention group also used TCPMs based on syndrome differentiation. Incident diabetes and normalization of blood glucose are indexes of end point. Safety assessments and adverse event monitoring will also be conducted. The treatment duration is set for 24 weeks, and we will follow-up for another 2 years. *Discussion*. This trial may provide initial evidence regarding the efficacy and safety of TCPMs plus lifestyle intervention (LI) compared to LI alone for preventing T2DM and provide a comprehensive intervention plans that choose suitable TCPMs for diabetes prevention according to syndrome differentiation. *Trial Registration Number.* Chinese Clinical Trial Registry ID: ChiCTR1900023541, registered on 1 Jun 2019. The version identifier is 2018121702.

## 1. Background

Type 2 diabetes mellitus (T2DM) and its precursor prediabetes are growing public health concerns. In China, it is estimated that one-third of the adult population have prediabetes, and experts have projected that more than 470 million people will have prediabetes by 2030 [1, 2]. Prediabetes is characterized by both mild impaired fasting blood glucose (IFG) and/or impaired glucose tolerance (IGT). People with IGT show normal fasting plasma glucose values (FBG less than 7.0 mmol/L) and abnormal two-hour postprandial blood glucose values (2h PG 7.8 to 11.0 mmol/L). People with IFG only demonstrate an abnormal FBG values (FBG 6.1 to 6.9 mmol/L; 2h PG less than 7.8 mmol/L, if measured). Prediabetes perpetuates pancreatic *β*-cell dysfunction and nearly always precedes T2DM. Furthermore, prediabetes and T2DM often accompany overweight/obesity and dyslipidemia, which are responsible for increased risk of all-cause mortality, cardiovascular disease, and stroke [3]. Therefore, the prevention of T2DM in prediabetic patients is a topic of importance. Guidelines for the prevention and control of T2DM in China recommend that lifestyle interventions and weight loss can prevent prediabetes progress to T2DM [4]. However, prediabetic individuals feel difficult to change their lifestyle, and the challenges also posed in successful implementation and maintenance of certain lifestyle modifications. The pharmacological options recommended in the guidelines for prediabetes are limited.

Currently, there are more than 100 TCPMs used for preventing and treating T2DM, and several systematic reviews have demonstrated that TCPMs combined with moderate lifestyle modification may reduce the risk of progression to T2DM and increase the possibility of regression toward normoglycemia [5, 6]. TCPMs contain various active ingredients, which possess different efficacies and therapeutic principles. In the process of TCM clinical practice, a comprehensive analysis of symptoms and signs is conducted which has implications for determining the cause, nature, and location of the illness and the patient's physical condition and eventually deciding which kinds of TCPMs they should use. Here, our research team will implement a multicenter, prospective cohort study to investigate the efficacy and safety of TCPMs in the prevention of T2DM on the basis of syndrome differentiation and treatment. This work describes the methodology and specific details underlying the study.

## 2. Methods

### 2.1. Trial Design

This study is a multicenter cohort study with two arms. A total of 600 participants will be recruited. The participants will be divided into either intervention or control groups according to their own desire, and the exposure factor is the application of TCPMs. All participants will be encouraged to lead a healthy lifestyle, and the intervention group also used TCPMs based on syndrome differentiation. Incident diabetes and normalization of blood glucose are indexes of end point. Safety assessments and adverse event monitoring will also be conducted. The treatment duration is set for 24 weeks, and we will follow-up for another 2 years.

### 2.2. Ethics, Consent, and Permissions

Approval of protocol and informed consent forms (CRFs) by the local institutional review board was obtained at Guang'anmen Hospital of the China Academy of Chinese Medical Sciences (2019-011-KY). The trial protocol registration number is as follows: Chinese Clinical Trial Registry no. ChiCTR1900023541, and any important changes in the protocol will be reflected there. The trial will be conducted in accordance with the principles of the Declaration of Helsinki (2013 version). When we design the protocol of this study, we refer to the statement of Consolidated Standards of Reporting Trials (CONSORT) and CONSORT Extension for Chinese Herbal Medicine Formulas [7]. We will distribute the CRFs to all participants before enrollment, which will be helpful of understanding the content of these trials and the benefit and harm of this trial. The trial will be completed according to the Standard Protocol Items: Recommendations for Intervention Trials (SPIRIT) guidelines [8]. The trial flow diagram is illustrated in Figure 1.

### 2.3. Study Population and Recruitment

A total of 600 participants will be recruited from six hospitals in mainland China, including Guang'anmen Hospital of the China Academy of Chinese Medical Sciences, Beijing Shijitan Hospital, Capital Medical University, Beijing Changping District Hospital of Chinese Medicine, Beijing Shunyi District Hospital of Chinese Medicine, Beijing Miyun District Hospital of Chinese Medicine, and Beijing Pinggu District Hospital of Chinese Medicine. The participants will be divided into either the intervention group or the control group (1 : 1). Participants should be included according to the diagnostic criteria and inclusion criteria and should be refused according to the exclusion criteria. Eligibility criteria are listed as follows.

### 2.4. Eligibility Criteria

#### 2.4.1. Diagnostic Criteria

Impaired glucose tolerance (IGT) is defined according to the 1999 WHO criteria: FBG <7.0 mmol/L or 2h PBG ≥7.8 and <11.1 mmol/L.

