#### 2.4.4. Exclusion Criteria

Participants who had acute cardiovascular events, myocardial infarction, or stroke within the past 6 monthsParticipants with serum transaminase level two times higher than the upper limit of normal value and serum creatinine two times higher than the upper limit of normal valueParticipants whose blood glucose rise is caused by a stress state or secondary reasonParticipants with psychiatric conditionsPregnant, lactating women, or having a history of drug allergyParticipants with severe cardiovascular and respiratory disease or severe complications of the liver, kidney, brain, or other primary diseasesParticipants who suffered acute infections and severe infectionsParticipants who have used hypoglycemic drugs in the past 3 months

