### 2.6. Outcome Measurement

#### 2.6.1. Indexes of End Point

Incident diabetes according to the guideline for the prevention and treatment of type 2 diabetes (2017 edition)Normalization of Blood Glucose, FPG <5.6 mmol/L or 2h PBG <7.8 mmol/L

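### The IGT entry rule in section 2.4.1 joins its fasting and 2-hour limits with 'or', contradicts the Background definition, and admits people who do not have IGT

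*Protocol article*

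**What the plan says.** The eligibility definition in section 2.4.1 opens "Impaired glucose tolerance (IGT) is defined according to the 1999 WHO criteria: FBG <7.0 mmol/L or 2h PBG", and its limits in full are "FBG <7.0 mmol/L or 2h PBG ≥7.8 and <11.1 mmol/L".

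The Background (section 1) describes people with IGT as having "normal fasting plasma glucose values (FBG less than 7.0 mmol/L) and abnormal two-hour postprandial blood glucose values (2h PG 7.8 to 11.0 mmol/L"). It treats isolated IFG as a separate state: "FBG 6.1 to 6.9 mmol/L; 2h PG less than 7.8 mmol/L, if measured".

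Section 2.3 makes the diagnostic definition part of the entry rule: "Participants should be included according to the diagnostic criteria and inclusion criteria". Section 2.4.3 then requires the IGT criteria to be met twice, at entry and again after a month of diet and exercise.

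The only glucose-related exclusions in section 2.4.4 are hyperglycaemia from stress or a secondary cause, and use of hypoglycaemic drugs in the past 3 months. Neither sets a glucose value.

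Section 2.6.1 lists two endpoints. Incident diabetes is defined by reference to a 2017 guideline. The other is "Normalization of Blood Glucose, FPG <5.6 mmol/L or 2h PBG <7.8 mmol/L".

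**The concern.** Both definitions cannot hold. With 'or', the first limb alone (FBG below 7.0) is enough, whatever the 2-hour value. The second limb alone is also enough, whatever the fasting value. The retest after a month applies the same rule, so it removes nobody whom the rule wrongly admits.

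This matters because both endpoints in section 2.6.1 are defined as leaving IGT, in one direction or the other. Someone who is not in that state at week 0 cannot make either transition in the intended sense. Groups are also formed by participants' own wishes (section 2.1), so a mixed entry population need not be balanced between the arms.

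The planning rates in section 2.10 are conversion rates from IGT to T2DM. They do not describe a cohort that includes people with normal glucose.

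**Working it through.** **Step 1. The two rules side by side**

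- Section 2.4.1: FBG < 7.0 OR (7.8 ≤ 2h PBG < 11.1).
- Background: FBG < 7.0 AND 2h PG from 7.8 to 11.0.
- Normalization endpoint, section 2.6.1: FPG < 5.6 OR 2h PBG < 7.8.

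The glucose pairs below are test values chosen for this check, in mmol/L.

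| FBG / 2h PBG | State | 2.4.1 ('or') | Background ('and') | Normalized at baseline |
|---|---|---|---|---|
| 5.0 / 6.0 | normal | qualifies | fails | yes |
| 6.5 / 7.0 | isolated IFG | qualifies | fails | yes (2-hour limb) |
| 6.0 / 9.0 | IGT | qualifies | qualifies | no |
| 8.0 / 9.0 | FBG ≥ 7.0, 2h in band | qualifies | fails | no |
| 6.5 / 13 | FBG < 7.0, 2h ≥ 11.1 | qualifies | fails | no |
| 7.5 / 12.0 | both above limits | fails | fails | no |
| 7.2 / 7.0 | FBG ≥ 7.0, 2h < 7.8 | fails | fails | yes (2-hour limb) |

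Four kinds of entrant pass section 2.4.1 and fail the Background definition. The last two rows show that a fasting value of 7.0 or above does not qualify by itself; the 2-hour value must also lie in the band.

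**Step 2. Illustration of dilution (incident diabetes)**

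Inputs from section 2.10: annual conversion of 10% (control) and 5.7% (TCPM), and 300 per group. The alpha of 0.05 is taken as two-sided, following section 2.11. Assumed here and not in the document: a 30-month horizon (24 weeks plus 2 years, about 2.5 years), no dropout, 1% annual conversion in normoglycaemic control entrants, and the same risk ratio in everyone.

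- Control risk in IGT: 1 − 0.90^2.5 = 0.2316.
- TCPM risk in IGT: 1 − 0.943^2.5 = 0.1365. Risk ratio: 0.1365 / 0.2316 = 0.589.
- Control risk in normoglycaemic entrants: 1 − 0.99^2.5 = 0.0248.
- With share g normoglycaemic: p1 = (1 − g) × 0.2316 + g × 0.0248, and p2 = 0.589 × p1.
- Power = Φ{[(p1 − p2)√300 − 1.96√(2p̄(1 − p̄))] / √[p1(1 − p1) + p2(1 − p2)]}, where p̄ is the mean of p1 and p2.

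| g | p1 | p2 | Power |
|---|---|---|---|
| 0 | 0.232 | 0.136 | 85% |
| 10% | 0.211 | 0.124 | 81% |
| 20% | 0.190 | 0.112 | 76% |
| 30% | 0.170 | 0.100 | 71% |

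**Step 3. Dependence on the horizon**

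On one-year rates with the one-sided 0.05 test of section 2.10, power at 300 per group is 62% with no normoglycaemic entrants. It falls to 58%, 53% and 47% at shares of 10%, 20% and 30%, here assuming 1% conversion in normoglycaemic entrants of both arms. The direction is the same, but the level depends on the construct chosen.

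**The case against.** The strongest reply is that 'or' is a one-word slip in a condensed article. Section 2.4.1 names IGT and cites the 1999 WHO criteria, section 2.4.3 asks for IGT twice, and the Background gives the intended meaning. Read literally, the first limb would call every adult with FBG below 7.0 a case of IGT, which no centre is likely to apply. Nothing shown proves that the screening forms carry the same wording.

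This is plausible, and it limits what can be claimed about actual enrolment. It does not remove the contradiction. The faulty wording stands in the eligibility section, which six hospitals are to apply, and nothing else in the criteria corrects it.

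Three stronger readings might be inferred, and the document does not support them:

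- *Everyone with fasting glucose of 7.0 or above gets in.* They qualify only if the 2-hour value is 7.8 to below 11.1.
- *Entrants above the limits will certainly be counted as incident cases.* Section 2.6.1 defers the diabetes definition to a guideline that is not shown, so only 'may' is justified.
- *The plan loses a known amount of power.* The shares, the 1% rate and the 30-month two-sided construct are assumptions; section 2.10 plans on annual rates with a one-sided test. The figures also concern incident diabetes, whereas the primary outcome in section 2.6.2 is change in FBG, 2h PBG and HbA1c, for which no effect is quantified here.

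A reader might also see a similar problem in section 2.4.4, where two laboratory limits are joined by 'and'. That phrase reads naturally as a list of two excluded groups and is not part of this point.

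**Conclusion.** The entry rule is wrong as written. It contradicts the document's own definition of IGT, and it is the rule that decides who enters. This conclusion rests on the text alone and needs no assumed figure.

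The firmest consequence also follows from the text: entrants with normal glucose or isolated IFG satisfy the normalization endpoint before any treatment. Entrants above the IGT limits may already satisfy the diabetes endpoint, and the planning rates do not apply to either kind of entrant.

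The fall in power from about 85% to between 81% and 71% illustrates the direction and rough scale under the stated assumptions. It is not an estimate of what will happen, since the document gives no basis for the share of such entrants.

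**What to change.** - In section 2.4.1, replace 'or' between the fasting and 2-hour limits with 'and', so that it agrees with the Background: FBG <7.0 mmol/L and 2h PBG ≥7.8 and <11.1 mmol/L.
- Apply that rule at both qualifying assessments in section 2.4.3, and check that the screening forms at all six hospitals carry it.
- Exclude from the incident-diabetes risk set anyone outside these limits at week 0. If recruitment has begun, report how many there are in each group.

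One limit remains. The normalization endpoint has its own 'or', so a person with IGT at 5.2/9.0 would still count as normalized at baseline through the fasting limb. Correcting section 2.4.1 removes the entrants without IGT but not that case.

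The cost is a one-word amendment, a check of the screening forms, and slightly slower recruitment than the looser wording would allow.

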#### 2.4.2. TCM Syndrome Pattern Differentiation

TCM syndrome pattern differentiation is referred to the Diabetes Evidence-based Clinical Practice Guideline in TCM [9] and guidelines delineated in the Clinical Research of New Investigational Drugs in Traditional Chinese Medicine [10].Syndrome of dampness-heat accumulation in the spleen: dry mouth and thirst, sweet taste in the mouth, abdominal distension, the subjective sensation of heaviness of the body with difficult movement, and yellow urine, and patients usually have a red tongue with yellow, thick, and dry coating and a rapid strong pulseSyndrome of spleen deficiency and phlegm obstruction: overweight or obesity, abdominal obesity, lack of strength, poor appetite, loose stool, bland taste or sticky and greasy sensation in the mouth, pale scalloped tongue, white and greasy coating, and soggy and moderate pulseSyndrome of liver depression and qi stagnation: medium or thin shape, dry mouth and thirst, depressed mood frequent sighing, nervousness, distention, fullness in the chest and flank, dry stool, light red tongue, enlarged tongue body, white and thin coating, and stringy pulseQi-yin dual insufficiency syndrome: emaciation of the body, fatigue spirit and lack of strength, dry throat and mouth, thirst even with a large intake of fluid, feeling vexing heat in the five centers (chest, palms, and soles), spontaneous and night sweats, shortness of breath and reluctance to speak, palpitations, insomnia, a red tongue with scant liquids and thin white dry tongue coating, and a thread rapid pulse

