#### 2.4.3. Inclusion Criteria

Participants should be between 18 and 70 years of ageParticipants should meet the diagnostic criteria for IGTAfter a month of routine diet and exercise intervention, participants should meet the diagnostic criteria for IGTOverweight or obesity, body mass index (BMI) ≥  24 kg/m^2^According to syndrome pattern differentiation referred to the Diabetes Evidence-based Clinical Practice Guideline in TCM and guidelines delineated in the Clinical Research of New Investigational Drugs in Traditional Chinese MedicineParticipants should sign informed consent forms

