### 2.5. Interventions

The participants will be divided into either the intervention group or the control group (1 : 1). The control groups will conduct lifestyle intervention alone, and the intervention group will use TCPMs on the basis of lifestyle intervention.

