#### 2.5.2. Syndrome Differentiation of Traditional Chinese Patent Medicine

The intervention group will use TCPMs based on syndrome differentiation. If the syndrome belongs to dampness-heat accumulation in the spleen, it should be treated with JinQi-Jiangtang tablet (3 tablets, three times per day). If the syndrome belongs to spleen deficiency and phlegm obstruction, it should be treated with Shenzhu Tiaopi granule (2 bags, three times per day). If the syndrome belongs to liver depression and qi stagnation, it should be treated with Yue Ju pills (1 bag, three times per day). If the syndrome belongs to qi-yin dual insufficiency, it should be treated with Qizhi jiangtang capsule (2.5 g three times per day).

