### 2.10. Sample Size Calculation

According to previously published research [11], the annual conversion rate of IGT into T2DM was 1.5% in the TCM group and 10% in the control group. We predicted that the annual conversion rate of IGT into T2DM was 5.7% in the TCM comprehensive intervention group. Therefore, assuming that *α* = 0.05 and *β* = 0.1 according to the one-sided test, u*α* = 1.645 and u*β* = 1.282, and the data will be placed in the formula to obtain *n* = 299.94. Therefore, each group needs more than 300 participants, for a total of 600 participants.

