We hypothesize that the prediabetic patients will benefit from TCPMs. If successful, this trial may provide comprehensive intervention plans that choose suitable TCPMs for diabetes prevention according to syndrome differentiation. Although clinical trials are strictly designed, there might also be potential limitations. Firstly, there is no placebo in the control group. Secondly, the long treatment and follow-up period may lead to poor patient compliance, which might greatly influence the therapeutic effect. More effort should be made to find a solution in future trials.

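### The BMI ≥24 entry rule contradicts the written description of one syndrome and fits poorly with another, and the stated pooled analysis can test the syndrome-guided strategy but not whether each TCPM suits its syndrome

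*Protocol article*

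**What the plan says.** All references are to the protocol article.

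- **Entry (2.4.3).** All participants must be overweight or obese, with BMI ≥24 kg/m². The same list contains a syndrome item: "According to syndrome pattern differentiation referred to the Diabetes Evidence-based Clinical Practice Guideline in TCM".
- **Syndromes (2.4.2).** Qi-yin dual insufficiency opens with "emaciation of the body, fatigue spirit and lack of strength". Liver depression and qi stagnation opens with a medium or thin build. Spleen deficiency and phlegm obstruction opens with overweight or obesity. Dampness-heat accumulation has no weight term; the nearest wording is "abdominal distension, the subjective sensation of heaviness of the body with difficult movement".
- **Treatment (2.5.2).** "The intervention group will use TCPMs based on syndrome differentiation". Each of the four syndromes is tied to a different product.
- **Groups (2.1, 2.5).** Two arms, stated as 1:1, formed by the participants' own wish. The exposure is use of TCPMs.
- **Sample size (2.10).** Two whole groups of 300. The inputs are "the annual conversion rate of IGT into T2DM was 1.5% in the TCM group and 10% in the control group" from earlier research, and "We predicted that the annual conversion rate of IGT into T2DM was 5.7% in the TCM comprehensive intervention group".
- **Analysis (2.11).** Chi-square, t, Fisher and Wilcoxon tests between the groups. No syndrome strata are named.
- **Aim (abstract and section 3).** If the trial succeeds, "this trial may provide comprehensive intervention plans that choose suitable TCPMs for diabetes prevention according to syndrome differentiation".

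**The concern.** Section 2.4.2 uses build to help tell syndromes apart, and the syndrome then fixes the drug. If the entry rule excludes the build by which a syndrome is described, there are two possibilities. Few people receive that syndrome label and its drug, or investigators at six hospitals assign the label against the written description, perhaps differently from site to site. In either case the meaning of the intervention arm depends on how the conflict is settled in practice, and the article does not say how.

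The second part concerns what the analysis can support. A comparison of all TCPM users with all controls averages over four products in whatever proportions happen to be enrolled. Because participants choose their arm, syndrome mix may also differ between arms. If it is related to diabetes risk, the named tests do not account for it. A favourable pooled result could be read as support for four drug-syndrome pairings, some of which may have been barely studied.

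**Working it through.** **Step 1. Entry rule against syndrome description.**

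| Syndrome (2.4.2) | Build described | Against BMI ≥24 (2.4.3) |
|---|---|---|
| Dampness-heat accumulation | none stated | no conflict |
| Spleen deficiency, phlegm obstruction | overweight or obese | agrees |
| Liver depression, qi stagnation | medium or thin | poor fit; medium is not an outright conflict |
| Qi-yin dual insufficiency | emaciated | direct contradiction |

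So one of four descriptions contradicts the rule and one fits it poorly. Section 2.4.2 does not say that every listed feature must be present.

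**Step 2. The plan's own sample size.** The article gives n = 299.94 per group, with u = 1.645 and 1.282. The unpooled formula on the stated annual rates is

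n = (1.645 + 1.282)² × (0.10 × 0.90 + 0.057 × 0.943) / (0.10 − 0.057)² = 8.567 × 0.14375 / 0.001849 = 666.

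The annual rates therefore do not reproduce 299.94. Doubling both rates to two years (20% and 11.4%) gives 302, which is close, but the article does not state that step. The present point does not rest on this figure. What matters here is that the calculation concerns two whole groups and makes no allowance for syndromes.

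**Step 3. Precision within one syndrome (illustration).** The article gives no syndrome mix. Assume an even split: 600 / 4 = 150 per syndrome, 75 per arm. Tests are two-sided at 0.05, as in 2.11.

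*One-year rates, 10% and 5.7%:*
- SE = √[(0.10 × 0.90 + 0.057 × 0.943) / 75] = √(0.14375 / 75) = 0.0438
- Power = Φ(0.043 / 0.0438 − 1.96) = Φ(−0.98) ≈ 16%

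*Rates compounded to 30 months, the last visit in Table 1:*
- Control: 1 − 0.90^2.5 = 23.16%. TCPM: 1 − 0.943^2.5 = 13.65%. Difference: 9.5 points
- SE = √[(0.2316 × 0.7684 + 0.1365 × 0.8635) / 75] = 0.0628
- 95% half-width = 1.96 × 0.0628 = 12.3 points
- Power = Φ(0.0951 / 0.0628 − 1.96) = Φ(−0.45) ≈ 33% (32% with a pooled-variance formula)

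**Step 4. Sensitivity to the assumed split** (pooled-variance formula, one-year rates to 30 months):

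| Per arm in the syndrome | Power |
|---|---|
| 25 | 8% to 14% |
| 75 | 16% to 32% |
| 150 | 28% to 57% |

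For 80% power a single syndrome would need about 613 per arm on one-year rates or 260 per arm on 30-month rates. Both far exceed 75.

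**The case against.** The strongest reply is that the trial evaluates a strategy: TCPM chosen by syndrome, plus lifestyle intervention, against lifestyle intervention alone. The exposure is defined as use of TCPMs, and section 3 presents individual drug choice as a deliberate match to practice. For that question a pooled comparison is natural. No drug-specific hypothesis or test is stated. This stands.

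Several stronger readings are tempting but not supported.

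- A reader might infer that two of the four syndromes are closed to overweight people and will be nearly empty. Liver depression allows a medium build, build is not said to be obligatory, the guidelines cited for classification are not at hand, and no syndrome mix is given. Sparse strata are a risk, not a known outcome.
- A reader might infer that a planned syndrome-specific conclusion is impossible. None is planned. The closing claim is conditional and says only what the trial may provide.
- A reader might count the lack of named strata or an interaction test as an omission. A journal article commonly leaves these to the analysis plan, which is not shown. The point here is narrower: the tests the article does name are unadjusted.
- A reader might take the power figures as the trial's power on its primary outcome. They concern incident diabetes, whereas the primary outcome is change in FBG, 2h PBG and HbA1c.

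It is also fair to say that recording of syndrome among controls is an inference from a fragmentary inclusion item, since Table 1 has no row for syndrome classification. Stratifying by syndrome would deal with only one of the possible confounders in a self-selected cohort.

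**Conclusion.** The point holds in a limited form. The BMI rule contradicts the qi-yin description and fits poorly with the liver-depression description. Because syndrome decides the drug, the conflict reaches both eligibility and treatment assignment, and the passages must be reconciled. The documents do not show which should govern.

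The stated unadjusted comparison can address the syndrome-guided strategy as a whole, subject to confounding by self-selection. It cannot show that each TCPM suits its syndrome. The sample would support such a claim weakly even under an even spread: about 16% to 33% power within a syndrome for incident diabetes. That range assumes equal strata, the article's annual rates in every syndrome and, at the upper end, that those rates continue for 30 months, about two years of which follow the 24-week drug period. Smaller strata would do worse. This is a correction worth making before analysis; it does not invalidate the overall comparison.

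**What to change.** 1. Reconcile the BMI criterion in 2.4.3 with the two syndrome descriptions in 2.4.2. State which features are required for classification and how a participant who meets one text but not the other is handled. The choice belongs to the investigators.
2. Confirm that syndrome is recorded at entry, before the arm is chosen, in both arms, and add it to Table 1.
3. Use syndrome as a stratification factor in the pooled comparison, for example Mantel-Haenszel for incident diabetes and a model with syndrome as a covariate for the glucose measures. If the analysis plan already does this, align 2.11 with it.
4. Report the number enrolled per syndrome and arm, and syndrome-specific estimates with intervals against controls of the same syndrome, labelled exploratory.
5. In the abstract and section 3, limit the conclusion to the overall strategy and to the syndromes actually enrolled in number.

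The cost is a protocol clarification that touches eligibility, slightly more analysis and a narrower claim. No new data are needed if syndrome is already recorded for controls; if it is not, one entry item has to be added.
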